## Abstract

**Background:**

Coronary artery disease (CAD) remains a severe socio-economic burden in the Western world. Coronary obstruction and subsequent myocardial ischemia result in the progressive replacement of contractile myocardium with dysfunctional, fibrotic scar tissue. Post-infarctional remodelling is causal for the concomitant decline of left-ventricular function and the fatal syndrome of heart failure. Available neurohumoral treatment strategies aim at the improvement of symptoms. Despite extensive research, therapeutic options for myocardial regeneration, including (stem)-cell therapy, gene therapy, cellular reprogramming or tissue engineering, remain purely experimental. Thus, there is an urgent clinical need for novel treatment options for inducing myocardial regeneration and improving left-ventricular function in ischemic cardiomyopathy. Shockwave therapy (SWT) is a well-established regenerative tool that is effective for the treatment of chronic tendonitis, long-bone non-union and wound-healing disorders. In preclinical trials, SWT regenerated ischemic myocardium via the induction of angiogenesis and the reduction of fibrotic scar tissue, resulting in improved left-ventricular function.

**Methods:**

In this prospective, randomized controlled, single-blind, monocentric study, 80 patients with reduced left-ventricular ejection fraction (LVEF≤ 40%) are subjected to coronary-artery bypass-graft surgery (CABG) surgery and randomized in a 1:1 ratio to receive additional cardiac SWT (intervention group; 40 patients) or CABG surgery with sham treatment (control group; 40 patients). This study aims to evaluate (1) the safety and (2) the efficacy of cardiac SWT as adjunctive treatment during CABG surgery for the regeneration of ischemic myocardium. The primary endpoints of the study represent (1) major cardiac events and (2) changes in left-ventricular function 12 months after treatment. Secondary endpoints include 6-min walk test distance, improvement of symptoms and assessment of quality of life.

**Discussion:**

This study aims to investigate the safety and efficacy of cardiac SWT during CABG surgery for myocardial regeneration. The induction of angiogenesis, decrease of fibrotic scar tissue formation and, thus, improvement of left-ventricular function could lead to improved quality of life and prognosis for patients with ischemic heart failure. Thus, it could become the first clinically available treatment strategy for the regeneration of ischemic myocardium alleviating the socio-economic burden of heart failure.

**Trial registration:**

ClinicalTrials.gov NCT03859466. Registered on 1 March 2019.

## Introduction

### Background and rationale {6a}

Myocardial viability dictates survival and functional improvement after coronary artery bypass grafting (CABG) in patients with postischemic congestive heart failure [1, 2]. The success of surgical revascularisation is limited by non-viable myocardium. Therefore, adjunctive therapies inducing myocardial regeneration, applied during surgery, could improve survival and functional outcome in patients with postischemic congestive heart failure. To gain broad clinical applicability, adjunctive myocardial regenerative therapies must be efficient, easily applicable and safe.

Various cell lines, including autologous myoblasts and stem cells, induce myocardial regeneration when applied in adjunction to coronary artery bypass grafting [3, 4]. However, the production of cells is complex, carries a significant financial burden and can be accompanied by serious adverse events [5, 6].

Shock wave therapy has been used to treat kidney stones for the past 20 years [7]. If applied at low energy levels, shock waves can regenerate infarcted and chronic ischemic myocardium. Shock waves can be delivered percutaneously or direct epicardially. Percutaneous cardiac shock wave therapy improves clinical symptoms in patients with chronic ischemic myocardium. However, percutaneous cardiac shock wave therapy is limited by appropriate acoustic windows — shock waves cannot safely be applied over lung tissue [8, 9]. Therefore, only selected areas of the myocardium — primarily the anterior wall — can be treated by percutaneous cardiac shock wave therapy. Direct epicardial shock wave therapy (DESWT) may develop as an adjunctive therapy to CABG, especially in those patients with large myocardial infarcts or areas of non-reversible ischemia. Up to date, no published data on DESWT exist [10].

The objective of the CAST-HF trial, therefore, is to evaluate the effect of direct epicardial shockwave therapy adjunctive to CABG surgery in patients suffering from markedly reduced ejection fraction. For this study, a newly developed device specifically designed for direct cardiac treatment will be tested.

### Objectives {7}

Primary:To assess the safety profile of the deviceTo assess the Improvement of left ventricular ejection fraction (LVEF) by using cardiac shock wave therapy in patients undergoing primary coronary artery bypass grafting and suffering from reduced left ventricular function below or equal 40%

Secondary:To assess the long-term safety profile of the deviceTo assess the long-term performance profile of the device

Exploratory:To evaluate gene expression profiles associated with cardiac shockwave therapy

### Trial design {8}

SPIRIT guidance: Description of trial design including type of trial (e.g. parallel-group, crossover, factorial, single group), allocation ratio, and framework (e.g. superiority, equivalence, noninferiority, exploratory).

The CAST-HF trial is a randomized, single-blind, parallel-group, sham-controlled superiority trial.

## Methods: Participants, interventions and outcomes

### Study setting {9}

All participants will be recruited by the medical specialist team supported by a study nurse (recruiting team) at the Department of Cardiac Surgery, Medical University Innsbruck (MUI) (Investigation Site). A data safety monitoring board (DSMB) consisting of external experts is established to review patient’s data for inclusion, exclusion or early study termination. All data will be collected by the research team consisting of physicians and healthcare researchers. Data analysis will be performed by the Department of Medical Statistics, Informatics, and Health Economics, Innsbruck Medical University, Innsbruck, Austria.

### Eligibility criteria {10}

Adult patients with postischemic heart failure undergoing coronary artery bypass grafting (CABG). All participants will undergo the usual standard medical work-up before, during, and after CABG according to the ESC/EACTS Guidelines on Myocardial Revascularization. This includes Coronary Angiography, Echocardiography, Spirometry, Carotid Artery Duplex Scan, Cardiac MRI, Computed Tomography, and interviews with the Cardiologist, Cardiac Surgeon, and Anesthesiologist.

Inclusion criteria:Male or female patients above 21 and under 90 years of age undergoing primary coronary artery bypass grafting.Patients have to present with reduced left ventricular function defined as LVEF ≤ 40%.Patients have to present with regional left ventricular wall motion abnormalities.Patients have to give written informed consent to participate in the study.

Exclusion criteriaSignificant concomitant aortic valve disease in need of surgical treatment (Except significant aortic valve disease not detected in preoperative cardiac ultrasound that is detected intra-operatively).Serious radiographic contrast allergy.Patients in cardiogenic shock or presenting with acute myocardial infarction (STEMI or NSTEMI)Patients with a contraindication for cardiac MRI (e.g. glomerular filtration rate <30ml/min/1.73m^2^)History of significant ventricular arrhythmias, except arrhythmias associated with MI.Present co-morbidity, which reduces life expectancy to less than 1 year.Presence of ventricular thrombus.Presence of a cardiac tumour.Pregnancy.

### Who will take informed consent? {26a}

Every patient must give his/her written consent before participating in the clinical trial. Before the patient gives his/her written consent, the patient has to be informed completely in oral and written form in an understandable manner about the patient about character, importance, relevance and consequences of the clinical trial by one of the study investigators whom the principal investigator specifically delegates.

The content of the consent information has to be documented on the Informed Consent. The patient will be notified if essential findings about the MD appear during the study.

The Informed Consent of the patient about participation in the clinical trial must be dated and signed by the patient and the study investigator. The patient receives one exemplar of the signed and dated Patient Information and Informed Consent Form. The investigator must store the second signed and dated exemplar in the Investigator Site File.

It must be explicitly pointed out that until valid Informed Consent of the patient is existent no study-specific investigations carried out with the patient are allowed.

### Additional consent provisions for collection and use of participant data and biological specimens {26b}

The following additional collections and use of participant data and biological specimens are explicitly stated in the informed consent file: left-ventricular biopsies, biosamples. Details on collection of these samples are described in section 33. Additionally, patients are informed in oral form and in an understandable manner about the character, importance, relevance and consequences of these collections.

## Interventions

### Explanation for the choice of comparators {6b}

The control group receives CABG surgery without DESWT, which is the state-of-the-art technique for the treatment of myocardial infarction due to coronary artery disease. Instead of DESWT, a Sham Treatment will be performed. For this reason, a non-functional applicator will be held on the exact same areas of the heart for the same amount of time, as the in patients of the treatment group. Thus, the control patients receive the same manipulation of the specific areas as the patients in the treatment arm.

### Intervention description {11a}

Both the experimental intervention and the sham procedure are performed during open, on-pump CABG surgery indicated by the institutional heart team of interventional cardiologists and cardiac surgeons.

#### Experimental (intervention) arm

In the intervention arm, 300 shockwave impulses per coronary supply territory, at an energy flux density of 0.38mJ/mm2 and a frequency 3Hz, are applied in direct contact with the ischaemic myocardium of the left ventricle. The intervention is performed during CABG surgery after bypasses are fully established while still on cardiopulmonary bypass by the same cardiac surgeon performing the CABG procedure whom the principal investigator delegates. No specific surgical skills are needed for the application of DESWT with the Cardiac Shockwave Probe; however, investigators performing the procedure are trained and supervised by both the principal investigator and technicians to ensure reproducibility.

The cardiac shockwave system consists of a table-top device (Nonvasiv Medical GmbH, Konstanz, Germany) and a sterile single-use applicator releasing electrohydraulic shockwaves (Heart Regeneration Technologies GmbH, Innsbruck, Austria). Prior to use, the applicator is inserted into a sterile cover containing ultrasound gel. In order to ensure acoustic coupling between the applicator and the myocardium, continuous saline rinsing is applied throughout the procedure.

#### No intervention (sham control) arm

In the sham control arm, the same manipulations are performed with an inactive shockwave applicator in direct contact with the ischaemic myocardium of the left ventricle as in the intervention arm. The sham treatment is performed during CABG surgery after bypasses are fully established while still on cardiopulmonary bypass.

### Criteria for discontinuing or modifying allocated interventions {11b}

Subjects will exit the clinical investigation for any of the following reasons:Screening failureWithdrawal of informed consentLost to follow-upDeath

The subject is free to withdraw its written informed consent at any time. The reason for withdrawal should, if available, be documented in the subject’s medical file and in the CRF. When a subject withdraws or is withdrawn from the clinical investigation, a final clinical evaluation should be performed, documented in the medical record and in the CRF.

A subject is not considered lost to follow-up until the full study period has elapsed. The investigator should try to contact the subjects at every follow-up until clinical investigation ends.

### Strategies to improve adherence to interventions {11c}

To improve adherence to the study protocol, the follow-up visits for the study are planned simultaneously with the standard clinical follow-up appointments for patients in the high-risk cardiac surgery program at the Department for Cardiac Surgery, Medical University of Innsbruck. Apart from showing up for the follow-up appointments, participants do not need to adhere to specific tasks.

### Relevant concomitant care permitted or prohibited during the trial {11d}

There is no expected interaction between the device under investigation and concomitant medical treatments.

Throughout the study, investigators are permitted to use their clinical judgement when prescribing concomitant medications and treatments for trial patients. Local prescribing information and institutional guidelines should be followed as applicable.

#### Optimized, guideline-directed medical therapy

This study is designed to be an all-comers study. Optimized medical therapy according to heart failure guidelines of the European Society of Cardiology (PMID: 34447992) may already be achieved at the time of screening and treatment or not. In any case, at the time of follow-up visits to assess LVEF via cardiac MRI (D180, D360) patients have to be on stable, guideline-directed medical therapy for at least 30 days prior to each visit.

This includes the following definitions according to the patients’ clinical presentation and the judgement of the responsible physician:No more than a 100% increase or a 50% decrease of the dosage of any one medication other than a diuretic.Medication changes within a drug class are allowed as long as the equivalent dosage is within the limits specified above.Unrestricted changes in diuretics are allowed as long as the subject remains on a diuretic.

### Provisions for post-trial care {30}

The Sponsor will take out reasonable third-party liability insurance cover in accordance with local legal requirements. The civil liability of the Investigator, all persons instructed and the hospital, practice or institute in which they are employed and the liability of the Sponsor in respect of financial loss due to personal injury and other damage that may arise as a result of the carrying out of this study are governed by the applicable local law.

As a precautionary measure, the Investigator, the persons instructed and the hospital, practice or institute are included in such cover in terms of their work done in carrying out the study to the extent that the claims are not covered by their own professional indemnity insurance.

The Sponsor will arrange for patients participating in this study to be insured against financial loss due to personal injury caused by the device being tested or by medical steps taken in the course of the study. Such insurance is taken out by the Sponsor in accordance with or by way of analogy to both the Austrian and the other participating countries’ drug law.

### Outcomes {12}

Primary endpoints:Efficacy: Improvement in LVEF measured by cardiac MRI from baseline to 360 days.Safety: Occurrence of device-related complications (adverse device effects or serious adverse device effects) within 360 days.

Secondary endpoints:Endpoints related to the efficacy are changes in the following parameters within a time frame of 360 days:6-min walk test distanceNYHA functional classSerum nt-proBNP levelsRenal function, measured by glomerular filtration rate (GFR)Seattle Angina Pectoris Questionnaire (SAQ)36-item short-form survey (SF36)Minnesota Living with Heart Failure Questionnaire (MLHFQ)Secondary safety-related endpoints include the following observations within a time frame of 6 days:Occurrence of ventricular arrhythmia during the hospital stayOccurrence of device-related peri-operative myocardial damage detected by a rise of cardiac biomarkers: creatine kinase (CK-MB) and troponin T (TropT)Occurrence of signs of device-related infection detected by a rise of C-reactive protein (CRP) or leukocytosis during the hospital stay

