## Assignment of interventions: blinding

### Who will be blinded {17a}

This study is single-blinded as the PI, and the surgical personnel involved in the study procedure (shockwave therapy or sham treatment) know the randomization arm. However, all study assessments will be performed in an observer-blinded fashion. Patients, the investigators performing the endpoint analyses, and data analysts are blinded to the group assignment.

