
#### Laboratory analysis

Samples of laboratory tests will be analysed at the local laboratory.

Blood analysis will be done as part of the regular safety assessments at baseline, at hospital discharge and at visits in the long-term follow-up.

The following parameters will be measured:Laboratory results general:LactatdehydrogenaseErythrocytesHaemoglobinHaematocritPlatelet countCRPLeukocytesThrombo testActivated partial thromboplastin timeInternational normalized ratioPro BNPLaboratory results heart enzymes:Total CKCK-MBCK-MB %Troponin T

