#### Safety and secondary analyses

Secondary and safety parameters will be summarized using descriptive statistics, i.e. number (%) of patients for categorical variables and mean, SD (standard deviation), median, minimum/maximum for continuous variables. Descriptive statistics will be produced by the treatment group. No formal hypothesis testing will be performed. Appropriate statistical tests will be applied in an explorative manner only. Occurrence of adverse events (safety) will be compared between treatment groups using chi-square tests and Fisher`s exact tests, as appropriate. Analyses of secondary endpoints will be analysed with appropriate statistical tests such as ANOVA for repeated measurements, paired and unpaired *t*-tests as well as their non-parametric equivalents.

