#### Adverse event reporting and harms {22}

An adverse event is the appearance or worsening of any undesirable sign, symptom, or medical condition occurring during or after the treatment (DESWT + CABG). Medical conditions/ diseases present before the treatment will only be considered adverse events if they worsen after the treatment. Abnormal laboratory values or test results constitute adverse events only if they induce clinical signs or symptoms, are considered clinically significant, or require therapy. The occurrence of adverse events should be sought (1) direct contact to the treating physicians, (2) screening of medical records and laboratory data for anticipated adverse events listed in the CRF and (3) by non-directive questioning of the patient at each visit during the study. Adverse events also may be detected when they are volunteered by the patient during or between visits or through physical examination, laboratory test, or other assessments.

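### The primary safety endpoint is named in two incompatible ways and analysed as a third quantity, and its device-related form is not stated to be judged blind to arm

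*Protocol article*

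**What the plan says.** Protocol article, by section:

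- **Abstract, Methods:** "The primary endpoints of the study represent (1) major cardiac events and (2) changes in left-ventricular function 12 months after treatment". Major cardiac events are not defined there or anywhere else.
- **Objectives {7}:** the primary safety aim is the device's safety profile; no event type is named.
- **Outcomes {12}:** the primary safety endpoint is "Occurrence of device-related complications (adverse device effects or serious adverse device effects) within 360 days". Neither death nor major cardiac events appears among the primary or secondary endpoints. Three secondary safety endpoints cover the first 6 days. Ventricular arrhythmia carries no attribution condition. Myocardial damage and infection must be device-related, and are detected by a rise of CK-MB and troponin T, or by a rise of CRP or leukocytosis.
- **Safety and secondary analyses:** "Occurrence of adverse events (safety) will be compared between treatment groups using chi-square tests and Fisher`s exact tests, as appropriate". The same paragraph states: "No formal hypothesis testing will be performed".
- **Adverse event reporting and harms {22}:** the definition given here reads: "An adverse event is the appearance or worsening of any undesirable sign, symptom, or medical condition occurring during or after the treatment (DESWT + CABG"). Relatedness to the device is not part of the definition.
- **Who will be blinded {17a}:** "This study is single-blinded as the PI, and the surgical personnel involved in the study procedure" know the arm. Patients, endpoint assessors and data analysts do not.
- **Interim analyses {21b}:** once at least 20 patients per group have completed 360 days for the primary endpoints, an analysis assesses safety and may end recruitment early.

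**The concern.** Safety is the first-listed aim, yet the article does not settle which events make up its primary safety endpoint. An all-cause cardiac endpoint, a causality-filtered device endpoint and a count of any adverse event can give different answers from the same data. With three candidates open, the reported one could be chosen after the results are seen, and the interim assessment of safety has no fixed input.

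The device-related version raises a second problem. Randomisation protects a comparison of all events between arms. It does not protect a comparison of events that have passed through a causality judgement, if whoever makes that judgement knows the arm. Such attribution can create an excess in the active arm or hide one by assigning events to the surgery. The two device-related biomarker endpoints pose a related problem, since surgery and device act on the same patient at the same time.

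**Working it through.** **Stated figures.** The article gives no event rate, margin or sample size for safety, so there is no safety figure to reproduce. Its one sample size adopted for the trial is for LVEF: d = (10.4 − 4.5)/8.7 = 0.678. With two-sided alpha 0.05 and power 0.80, the noncentral t gives 36 per arm, 72 in all, and 72/0.9 = 80. That reproduces the plan and has no bearing on this point.

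**Step 1: the three definitions side by side.** The abstract column takes the ordinary sense of the term, since the article defines none.

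| Event (illustrative) | Abstract: major cardiac event | Outcomes: device-related complication | Analysis: any adverse event |
|---|---|---|---|
| Post-operative infarction or cardiac death judged due to surgery | counts | does not count | counts |
| Minor injury from applicator contact | does not count | counts | counts |
| Non-cardiac illness unrelated to the device | does not count | does not count | counts |

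No two columns agree. The planned comparison therefore matches neither named endpoint.

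**Step 2: how far attribution could distort the device-related version.** Let r be the true risk of an adverse event, the same in both arms. Let f and g be the shares called device-related in the active and sham arms. The endpoint risks are r·f and r·g, so the spurious risk difference is r·(f − g). It is zero when f = g, which is what blind attribution would give when the arms have the same events.

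The abstract gives 40 per arm; r, f and g are assumptions, because the article supplies none. The last column is P = Σ Bin(i; 40, r·f) × Bin(j; 40, r·g), summed over pairs (i, j) with two-sided Fisher p ≤ 0.05.

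| r | f / g | Active / sham risk | Spurious difference | P |
|---|---|---|---|---|
| 20% | 30% / 30% | 6% / 6% | 0 | 0.01 |
| 20% | 30% / 0% | 6% / 0% | 6 points | 0.03 |
| 20% | 50% / 50% | 10% / 10% | 0 | 0.02 |
| 20% | 50% / 0% | 10% / 0% | 10 points | 0.21 |
| 40% | 30% / 30% | 12% / 12% | 0 | 0.02 |
| 40% | 30% / 0% | 12% / 0% | 12 points | 0.35 |
| 40% | 50% / 50% | 20% / 20% | 0 | 0.03 |
| 40% | 50% / 0% | 20% / 0% | 20 points | 0.84 |

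The rows with g = 0 are a deliberate extreme. Because safety testing is declared exploratory, P measures how often the arms would look different. It is not the error rate of a planned test.

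**Step 3: the biomarker endpoints.** Under Intervention description {11a}, both procedures take place during on-pump CABG, so every patient with a possible device effect also has the surgery, which can itself raise these markers. A rise in one patient therefore cannot be assigned to the device. A difference in post-operative levels between randomised arms can be, because the surgery is common to both.

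**The case against.** The best defence runs as follows. An abstract condenses, and the Outcomes section governs. A device-related endpoint fits the stated objective. The unfiltered comparison of adverse events is already planned, so an event called surgical would still be counted there. The blinding section says study assessments are observer-blinded, the unblinding section says device-related events can be processed without unblinding, and all captured adverse events go to an independent DSMB. Thresholds for a rise may sit in the full protocol.

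Much of this stands. It rules out the claim that safety goes unanswered, and it leaves room for blind attribution. It does not remove the contradiction: the article positively names two different primary endpoints and analyses a third. Nor does it say who judges relatedness, or that this person is blinded. A threshold would not separate device from surgery within a patient.

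A reader might infer more, in four ways that the document does not support:

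- **That the sham rate is near zero by construction, so no fair comparison is possible.** The inactive applicator is held on the same areas for the same time in direct contact, so contact or infection complications can occur in both arms.
- **That nearly every patient in both arms would meet the biomarker endpoints.** The article gives no such rate, and the device-related qualifier might exclude many.
- **That blood sampling misses early marker peaks.** Safety bloods are listed "at baseline, at hospital discharge and at visits in the long-term follow-up", but the visit schedule is not visible, and the biosample section draws blood at 4–12 h and 48–52 h.
- **That a fixed threshold measures the flaw.** At 40 per arm, 6 versus 0 gives Fisher p = 0.026 and 5 versus 0 gives 0.055; 0/40 has an exact two-sided upper 95% limit of 8.8%. The arithmetic is right. But the thresholds presuppose an empty sham arm and a decision rule that the plan disclaims, and 8.8% applies to any endpoint with no events in 40.

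**Conclusion.** The point holds as a contradiction in the definition of a primary endpoint. The abstract, the Outcomes section and the safety analysis use three different quantities, and the interim analysis leans on the primary endpoints. This conclusion needs no assumption beyond the text.

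The device-related version is open to attribution bias, because arm-aware staff are close to the judgement and blind attribution is not stated. The document does not show that such bias occurs, and its size cannot be derived from it. Under the assumed rates above with one-sided attribution, the spurious difference is 6 to 20 percentage points and P runs from 0.03 to 0.84. With equal attribution the difference is zero and P stays at or below 0.03.

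Inferring device-related damage or infection from a rise cannot work within a patient. The arrhythmia endpoint does not share this weakness.

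**What to change.** Before database lock, by the formal amendment that the article's section {25} requires for a substantial change:

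1. Reconcile the abstract, Outcomes and safety analysis to one defined primary safety endpoint, and list the events it contains.
2. Report major cardiac events, including death, and all serious adverse events to day 360 by randomised arm regardless of attribution, with the risk difference and an exact confidence interval.
3. Keep adverse device effects and serious adverse device effects as a descriptive listing. State who judges relatedness, and have it judged blind to arm where possible.
4. Replace counts of a rise with a between-arm comparison of post-operative CK-MB, troponin T and CRP levels, adjusted for baseline, at the sampling times the full protocol schedules.

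The cost is a documented amendment and a little more analysis. Adverse events are already captured, so the event comparison needs no new data. Recruitment closed on 01.06.2022 and the last visit was expected in April 2023, so the amendment should be dated and should say which results, including any interim results, had been seen.
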